### Re-intervention

No decision regarding re-intervention will be made before the 3-month follow-up. From this point, any recurrence of tributaries will be assessed from the patent’s history and a physical examination at the 3-, 6- and 12-month follow-ups. Re-intervention is indicated by the symptomatic recurrence of varicosities in the areas previously treated that are deemed to necessitate treatment by both the clinician and the patient. The method used for re-intervention will be chosen by the clinician who is caring for the patient.

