**Methods/design:**

This is a prospective single-centre randomised clinical trial. Patients with primary truncal vein incompetence and varicose vein tributaries requiring treatment will be assigned randomly to either ambulatory phlebectomies or foam sclerotherapy. The primary outcome measure is the re-intervention rate for the varicose vein tributaries during the study period. The secondary outcomes include the degree of pain during the first two post-operative weeks and the time to return to usual activities or work. Improvements in clinical scores, quality of life scores, occlusion rates and cost-effectiveness for each intervention are other secondary outcomes. The re-intervention rate will be considered from the third month.

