### Objectives

The primary objective is to ascertain the re-intervention rate following treatment with each modality. Pain score over the first 2 weeks will be assessed as a secondary objective using a 100-mm visual analogue scale and a numerical scale from 0 to 10. As additional secondary objectives, we will assess QoL, Venous Clinical Severity Score (VCSS), degree of bruising and phlebitis, patient satisfaction, time to return to normal activities and cost-effectiveness.

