### Primary outcome

The primary outcome of this study is the re-intervention rate at 12 months.

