### Blinding

After randomisation, at the point of the intervention, neither the patient nor the clinical team will be blinded to the allocation due to the nature of the intervention. However, following treatment, the clinicians conducting the follow-up reviews and the duplex ultrasound scan will be blinded to group allocation.

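### The primary endpoint is given two scopes, and its only operational rule ties the event to the area treated after allocation, so a tributary left untreated at the first session would not count

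*Protocol article*

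**What the plan says.** The primary endpoint appears in several places in the protocol article, with different scope.

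- Abstract, Methods/design: "The primary outcome measure is the re-intervention rate for the varicose vein tributaries during the study period". No area limit is given. The same paragraph adds "The re-intervention rate will be considered from the third month".
- Objectives: "The primary objective is to ascertain the re-intervention rate following treatment with each modality".
- Primary outcome: "The primary outcome of this study is the re-intervention rate at 12 months". Again no area is stated.
- Re-intervention: "Re-intervention is indicated by the symptomatic recurrence of varicosities in the areas previously treated", with the further condition "that are deemed to necessitate treatment by both the clinician and the patient". On timing, "No decision regarding re-intervention will be made before the 3-month follow-up".

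The order of events matters too. The Randomisation section has consent collected on the day of treatment and allocation after it. The Interventions section has the tributaries treated after allocation. The Blinding section says that, at the intervention, "neither the patient nor the clinical team will be blinded to the allocation due to the nature of the intervention"; the clinicians who do the follow-up reviews are blinded. The Eligibility criteria require tributaries that need treatment, but the article mentions no record of which tributaries these are before the arm is known.

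**The concern.** An endpoint that compares two techniques should be measured over an area that is the same whichever technique is drawn. The Re-intervention section instead refers to the treated area, which is itself a result of the procedure. If one technique leaves more of the needed work undone at the first session, the veins it leaves fall outside the area at risk. Their later treatment is then not an event, and the less complete technique looks better than it is.

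The stated objective is re-intervention after each modality, and incomplete first treatment belongs to that comparison. Neither safeguard in the plan reaches this. Blinded follow-up clinicians would be applying an area already set by an unblinded operator. Intention-to-treat analysis keeps every patient in the assigned arm, but it cannot restore events that the definition leaves out.

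**Working it through.** **Step 1: apply each passage to the same patient.**

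| Course after the index procedure | Abstract and Primary outcome | Re-intervention section |
|---|---|---|
| Vein treated, cleared, comes back with symptoms, treated at month 6 | Event | Event |
| Vein needed treatment at baseline, left untreated, treated at month 6 | Event (a tributary, within the study period) | Not an event (not in a treated area) |
| Vein treated, never cleared, treated at month 3 | Event | Unclear: area qualifies, but persistence may not be recurrence |
| Vein re-treated at week 8, elsewhere or as a deviation | Not counted under the Abstract's month-3 start | Should not arise under the plan |

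The second row is a direct conflict. The third is an ambiguity. The fourth should arise only outside the plan.

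**Step 2: reproduce the plan's own sample size.** Inputs from Sample size and study duration: 5% for phlebectomy (AP), 25% for foam sclerotherapy (FS), 80% power, 5% significance (taken as two-sided). The mean rate is 0.15.

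- Uncorrected: n = [1.96·√(2·0.15·0.85) + 0.8416·√(0.05·0.95 + 0.25·0.75)]² / 0.20² = 48.84, so 49 per group.
- Continuity-corrected: (48.84/4)·[1 + √(1 + 4/(48.84·0.20))]² = 58.41.

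The stated 58 per group matches the corrected formula up to rounding.

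**Step 3: sensitivity to missed events.** Evaluable patients: 160 × 0.70 = 112, or 56 per group. Power is the sum of the binomial probabilities of all pairs of event counts for which the uncorrected Pearson chi-squared test is significant at two-sided 5%. The share missed is an assumption, because the documents give none.

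| Assumed share of events missed | Observed rates, AP vs FS | Exact power |
|---|---|---|
| None | 5% vs 25% | 88.0% |
| 20%, both arms | 4% vs 20% | 78.4% |
| 20%, FS only | 5% vs 20% | 70.2% |
| 40%, both arms | 3% vs 15% | 63.8% |
| 40%, FS only | 5% vs 15% | 43.2% |

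The observed rates are the planned rates times one minus the share missed, for example 0.25 × 0.80 = 0.20. The starting value is above 80% because the uncorrected test is used, whereas the plan's 58 matches the corrected formula. If the 20% were lost in AP only (4% vs 25%), the same calculation gives 92%. In that case the definition would exaggerate the difference instead of hiding it.

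**The case against.** Five points can be made for the plan.

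1. The sentence in the Re-intervention section says when re-intervention is clinically indicated; it does not claim to define the endpoint. The Abstract and the Primary outcome section carry no area limit. This stands as far as it goes: a reader might infer that the trial counts only recurrence in treated areas, and the documents do not settle that. But no other passage gives a rule for deciding whether an event has occurred, so the two scopes remain in conflict.

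2. A reader might infer that never-cleared veins are excluded. That needs a strict reading of recurrence. A residual symptomatic vein lies in a treated area and would be seen at month 3 by a blinded clinician. It is an ambiguity, not a stated exclusion.

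3. A reader might infer that early re-treatment is scored as success. Under the plan it should not occur: Follow-up treatment periods and Re-intervention both rule out a decision before month 3, in both arms. Only a deviation or treatment elsewhere could produce it, and no rate is given.

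4. Eligible tributaries are identified in clinic before randomisation, and a condensed article may omit how they are recorded. The omission alone is therefore no finding. The point rests on the stated rule, which refers to the area treated and not to the veins identified at entry.

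5. A reader might infer that the definition dilutes the planned difference at the expense of FS detection. The documents do not say that either technique leaves target veins untreated, still less which one.

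**Conclusion.** The concern holds in a limited form. The primary endpoint has two scopes that give different answers for a patient later treated for a tributary left untreated at the first session. Under the only operational rule, the area at risk is determined after allocation by an unblinded operator. Whether a never-cleared vein counts is unclear.

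Neither the direction nor the size of any bias can be derived from the documents. The power figures show how sensitive a 5% versus 25% comparison is to missed events: from 88% to 78% if 20% are lost equally, or to 70% if lost in FS alone. They rest on assumed losses, 56 evaluable per group and a two-sided uncorrected chi-squared test, and are not an estimate of what will happen. The change should be made because it is cheap and removes a post-randomisation, operator-dependent element from the primary endpoint. The point does not show that the trial's result would be invalid.

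**What to change.** 1. Reconcile the Abstract, the Primary outcome section and the Re-intervention section so that one event definition applies throughout.
2. Record the target tributaries on a leg diagram before the online allocation is opened.
3. Define the primary event as re-intervention for a residual or recurrent varicosity within that pre-recorded area, up to 12 months. In the analysis, count any re-treatment that happens before month 3 as a deviation or elsewhere.
4. Keep recurrence within the area actually treated, from month 3, as a supportive analysis.
5. Leave the clinical rule on when re-intervention is decided as it is. The change concerns what is counted, not how patients are managed.

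The cost is one extra form and a change of wording, with no added visits or patients. The small downside is that some events will reflect incomplete first treatment and not true recurrence; the supportive analysis separates the two.

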### Randomisation

Signed written consent forms are collected on the day of treatment. Patients will then be randomised into one of the two possible treatment options by equal randomisation using an online computerised web system (SealedEnvelope, London, UK).

### Blinding

After randomisation, at the point of the intervention, neither the patient nor the clinical team will be blinded to the allocation due to the nature of the intervention. However, following treatment, the clinicians conducting the follow-up reviews and the duplex ultrasound scan will be blinded to group allocation.

### Data collection and confidentiality

All patient data will be stored in a password-protected Access database on a password-protected NHS computer at Imperial College London under the guidelines of the Data Protection Act 1998 and the EU General Data Protection Regulation 2016. Patient details will be anonymised as each participant will be allocated a study number. The codes for the allocated study numbers will be kept in the same database. The chief investigator will preserve the confidentiality of participants taking part in the study and is registered under the Data Protection Act.

Patient details, including contact information, will also be recorded on paper forms, such as the diary, questionnaires and clinical scoring sheets. These will be kept in a locked filing cabinet in a locked office for vascular research within the Vascular Surgery Section on Floor 4 North at Charing Cross Hospital (university office) for 10 years in accordance with Imperial College London’s policy. Each patient’s contact details will be discarded once they have been advised of the findings of the study (within approximately 6–12 months following completion of the study) Additional file 1.

### Publication of data

The findings from this study will be presented locally within the hospital, published in a peer-reviewed journal and presented at national and international conferences.

### Statistical analysis

Data collected from each patient will be entered into and analysed using the statistical software package SPSS version 24 (IBM, Armonk, New York, USA), STATA 15SE (STATACorp, College Station, Texas, USA) and Wizard Pro v1.9.29 (Evan Miller, Chicago, USA).

All analyses will be carried out on an intention-to-treat basis. To determine the normality of the data, both a visual test and a Shapiro–Wilk test will be used. If the data are normally distributed, the mean and standard deviation will be reported, otherwise the median and interquartile range. Categorial variables will be presented as frequencies and percentages. If the data are normally distributed, *t*-tests will be used or the Mann–Whitney *U* test if not. Assessments of the changes in scores from the baseline to each follow-up visit will be investigated using a repeated measures ANOVA. The primary outcome measure is a comparison of the re-intervention rates between groups at 12 months. This will be assessed with a Mann–Whitney *U* test.

The data will be assessed for missing values. The complete data set will be analysed using the listwise deletion methodology. The multiple imputation methodology will be used for missing data points.

Freedom from re-intervention curves will be analysed utilising survival analysis and Kaplan–Meier estimation methods with re-intervention classified as the failure event. Missing values for re-intervention due to loss to follow-up will be censored in the survival analysis.

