### Secondary outcomes

The secondary outcomes include:QoL scores at baseline, 2 weeks, 3 months, 6 months and 12 months using the EQ-5D, AVVQ and CIVIQ-14The clinical change in the VCSS from the baseline at 2 weeks, 3 months, 6 months and 12 monthsThe degree of bruising and phlebitis at 2 weeks (based on a clinical examination)The pain score over the first 2 weeksVisual (cosmetic) appearance at baseline, 2 weeks, 3 months, 6 months and 12 monthsThe time taken to return to work and normal activitiesPatient satisfaction at 2 weeks, 3 months, 6 months and 12 monthsCost-effectiveness

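### Secondary scores analysed as change from baseline by repeated-measures ANOVA give up precision, and listwise deletion and multiple imputation are both named without order or scope

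*Protocol article*

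**What the plan says.** The Secondary outcomes section of the protocol article lists "QoL scores at baseline, 2 weeks, 3 months, 6 months and 12 months" for the EQ-5D, AVVQ and CIVIQ-14, and the change in VCSS from baseline at the same four follow-ups.

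The Statistical analysis section makes these commitments:

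- Score analysis: "Assessments of the changes in scores from the baseline to each follow-up visit will be investigated using a repeated measures ANOVA".
- Missing data, in two consecutive sentences: "The complete data set will be analysed using the listwise deletion methodology" and "The multiple imputation methodology will be used for missing data points".
- Population: "All analyses will be carried out on an intention-to-treat basis".
- Normality: "To determine the normality of the data, both a visual test and a Shapiro–Wilk test will be used". The result decides between mean with SD and median with interquartile range, and between the t-test and the Mann–Whitney U test.

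The Follow-up treatment periods section has VCSS recorded at the follow-up visits. It provides reminders, and quality-of-life forms are posted when a visit is missed. The Sample size and study duration section expects about 30% drop-out and sets a total of 160 patients.

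**The concern.** The method for the scores is stated outright, so this is not detail left to another document. Three features of it matter.

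- **Baseline.** Subtracting the baseline score uses it with a coefficient of 1, whatever the data say. When baseline and follow-up are only moderately correlated, this over-corrects and adds noise to the between-arm comparison.
- **Missing visits.** Classical repeated-measures ANOVA needs a complete row per patient. Combined with listwise deletion, it excludes randomised patients who gave useful data at other visits. That sits badly with the intention-to-treat commitment and can bias the comparison if attendance depends on how the patient is doing. Multiple imputation would avoid the exclusion, but the section does not say which of the two methods carries the main result.
- **Test selection.** Separately, and of less weight, where t-tests or Mann–Whitney tests are used, a normality check on the trial data decides whether means or ranks are compared. Visits of one score could then be summarised or tested on different scales.

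At stake are the precision and interpretability of the VCSS and quality-of-life comparisons.

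**Working it through.** **Plan's own figures.** The article gives no sample size, SD or correlation for the scores. Its only calculation (58 per group) is for re-intervention and does not bear on this point. The inputs used from the article are the total of 160, equal allocation (80 per arm), about 30% drop-out and four follow-up visits.

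**Assumptions.** The SD σ is the same at baseline and follow-up. The correlation ρ between them runs from 0.3 to 0.8. One follow-up visit is considered at a time.

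**Step 1: precision of the two analyses.**

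- Change score: variance = σ² + σ² − 2ρσ² = 2(1−ρ)σ².
- Baseline-adjusted: variance = (1−ρ²)σ².
- Ratio, adjusted to change: (1−ρ²) / [2(1−ρ)] = (1+ρ)/2.

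| ρ | Change (σ²) | Adjusted (σ²) | Ratio | Variance saved | Patients needed by change score, relative to adjusted |
|---|---|---|---|---|---|
| 0.3 | 1.40 | 0.91 | 0.65 | 35% | 1/0.65 = 1.54 |
| 0.5 | 1.00 | 0.75 | 0.75 | 25% | 1/0.75 = 1.33 |
| 0.7 | 0.60 | 0.51 | 0.85 | 15% | 1/0.85 = 1.18 |
| 0.8 | 0.40 | 0.36 | 0.90 | 10% | 1/0.90 = 1.11 |

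Since 2(1−ρ) exceeds 1 when ρ is below 0.5, a change score is then less precise even than ignoring baseline.

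**Step 2: patients left under listwise deletion.** If drop-out of 30% is the only loss, 160 × 0.70 = 112 keep all four follow-ups, or 56 per arm. As an illustration only, if each visit were missed independently with probability m, the complete share is (1−m)⁴:

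| m (assumed) | (1−m)⁴ | Of 160 |
|---|---|---|
| 5% | 0.815 | about 130 |
| 10% | 0.656 | about 105 |
| 15% | 0.522 | about 84 |
| 20% | 0.410 | about 66 |

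**Step 3: detectable difference.** At one visit, with 80% power and two-sided 5%, in raw-score SD units: (1.960 + 0.842) × √(2/n) × √(variance factor from step 1). With n = 56, the first two terms give 0.53; with n = 80, 0.44.

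| ρ | Change, 56 per arm | Adjusted, 56 per arm | Adjusted, 80 per arm |
|---|---|---|---|
| 0.3 | 0.63 | 0.51 | 0.42 |
| 0.5 | 0.53 | 0.46 | 0.38 |
| 0.7 | 0.41 | 0.38 | 0.32 |

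The last column is the best case. A mixed model keeps patients with missing visits, but they contribute only partial information, so the truth lies between the last two columns.

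**The case against.** The strongest reply is that a reader might infer that the plan drops everyone who misses a visit. The article does not support that. The sentence after listwise deletion provides for multiple imputation, and with imputed visits a repeated-measures ANOVA keeps the patient. The two sentences can be read as a complete-case analysis plus an imputed one. This stands, and it limits the loss in step 2 to the listwise analysis. It does not settle which analysis is the main one.

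Posting missed questionnaires also protects EQ-5D, AVVQ and CIVIQ-14. That stands too. VCSS is recorded at clinical assessment, and the postal route does not recover it.

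It would also be too strong to say that the baseline value is wasted, or that the change-score comparison is biased. A change score does use baseline, and under randomisation it remains a valid comparison; the loss is one of precision. Nor does the article make the ANOVA depend on the normality check, which governs the summaries and the choice of t-test or Mann–Whitney and includes a visual check. It is an inference, not a statement, that these scores would be tested that way visit by visit.

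The magnitudes are assumed: no correlation or visit-level missingness is given, the formulas describe one visit, and the gain shrinks as ρ rises. That is why a range is shown.

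Finally, repeated-measures ANOVA is a recognised method, and covariance structure or sphericity correction may be left to a fuller document. That answers any complaint about missing detail. It does not answer the choice that the article has fixed, when a more precise analysis needs only data already planned.

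**Conclusion.** The point holds as one of efficiency and of an unresolved missing-data rule, for secondary outcomes only. Analysing change from baseline costs precision compared with baseline adjustment: adjustment lowers the single-visit variance by about 10% to 35% for ρ from 0.8 down to 0.3. This assumes equal variances; if they differ, the gain depends on how far the true regression slope is from 1. Listwise deletion and multiple imputation are both named with no order and no scope. Where listwise deletion is applied to the ANOVA, about 112 of 160 patients remain if the stated drop-out is the only loss, and fewer if other visits are missed as well.

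The normality-driven choice of test is a separate and lesser fault. A reader should not carry any of this over to the primary comparison of re-intervention, which does not use these scores. The change should be made, but the trial's main conclusion does not depend on it.

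**What to change.** 1. For each of VCSS, AVVQ, CIVIQ-14 and EQ-5D, make the primary score analysis a linear mixed model on all available follow-up visits. Use fixed effects for arm, visit (categorical), arm-by-visit and baseline score, with an unstructured covariance. Report the adjusted between-arm difference with 95% CI at each visit. VCSS can still be described as a change: once baseline is a covariate, modelling the follow-up score or the change gives the same between-arm difference.
2. State that this model rests on missing-at-random, and make multiple imputation the sensitivity analysis in place of listwise deletion.
3. Separately, fix the between-arm analysis of these scores in advance and do not let the Shapiro–Wilk result choose it. If residuals are skewed, use robust or bootstrap standard errors.

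The cost is a change of wording in the analysis section or the statistical analysis plan. No new data are needed, and SPSS 24 and Stata 15, both already named, fit the model.

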### Cost-effectiveness analysis

We will record equipment costs, the time for personnel to perform the interventions and the cost of the operating theatre. Time to return to work and the QoL gain following the procedure will be also assessed. The cost-effectiveness analysis will be undertaken with the aid of a specialist health economist.

### Data monitoring, safety and quality control

An adverse event is defined as any undesirable medical experience by a patient, whether or not it is related to the intervention. A severe adverse event (SAE) is a life-threatening experience. All adverse events should be documented and these reporting procedures should be followed. Queries should be directed to the chief investigator in the first instance. The chief investigator should be notified of all SAEs within 24 h. All SAEs should be reported to the research ethics committee if, in the opinion of the chief investigator, the event was related to the intervention. Reports of related and unexpected SAEs should be submitted within 15 days by the chief investigator, using the National Research Ethics Service SAE form for non-investigational medicinal product studies. Local investigators should report any SAEs as required by their local research ethics committee, the sponsor, and the research and development office. Imperial College London has public liability insurance to cover negligent harm and non-negligent harm arising from participation in this study. The study will be monitored and audited according to the policies of the Joint Research Compliance Office of Imperial College London.

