**Discussion:**

This study compares ambulatory phlebectomies and foam sclerotherapy in the treatment of varicose vein tributaries. The re-intervention rates, safety, patient experience and the cost-effectiveness of each intervention will be assessed. This study aims to recruit 160 patients and is expected to be completed by the end of 2019.

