## Abbreviations

AP: Ambulatory phlebectomy
AVVQ: Aberdeen Varicose Vein Questionnaire
CIVQ-14: Chronic Venous Insufficiency Questionnaire
EQ-5D: EuroQol Five-Domain Utility Index
FS: Foam sclerotherapy
QoL: Quality of life
SAE: Severe adverse event
VCSS: Venous Clinical Severity Score

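### The protocol's only SAE criterion is that an event threatens life, so hospitalising or disabling events that do not threaten life escape expedited reporting as written

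*Protocol article*

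**What the plan says.** The protocol article, under Data monitoring, safety and quality control, sets up two tiers of event.

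- **Lower tier.** It is broad: "An adverse event is defined as any undesirable medical experience by a patient, whether or not it is related to the intervention". The duty attached is: "All adverse events should be documented and these reporting procedures should be followed".
- **Upper tier.** It is defined in one sentence: "A severe adverse event (SAE) is a life-threatening experience". The abbreviation list expands the term the same way: "SAE: Severe adverse event".

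The escalation steps follow in the same section:

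- Internal notice: "The chief investigator should be notified of all SAEs within 24 h".
- Ethics committee: "All SAEs should be reported to the research ethics committee if, in the opinion of the chief investigator", the condition being that the event was related to the intervention.
- Time limit: "Reports of related and unexpected SAEs should be submitted within 15 days by the chief investigator", on a named national SAE form.
- Local reporting of SAEs, as the local ethics committee, the sponsor and the research and development office require.

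The Discussion part of the abstract lists safety among the things to be compared: "The re-intervention rates, safety, patient experience and the cost-effectiveness of each intervention will be assessed".

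**The concern.** *Severe* describes how intense an event is. Expedited reporting normally turns on whether an event is *serious*, which is judged by its outcome: death, threat to life, admission or prolonged admission, lasting disability, or other medical importance. The article uses the intensity word and then keeps only one of the outcome criteria.

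That one sentence controls all the escalation in the section. If it is too narrow, an admission or a lasting injury that never endangered life stays in the lower tier. The chief investigator need not hear of it within a day, and it does not reach the ethics committee even when it is related to the procedure. What is at stake is timely oversight of participants in a trial of two invasive treatments, and a consistent count of serious events in the final report.

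**Working it through.** No arithmetic applies, and the article gives no figure to reproduce. The check is to read the definition against each rule that depends on it, and then to look for wording elsewhere that widens it.

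**Step 1: the definition.** The safety section supplies one criterion, threat to life. The abbreviation list supplies the label *severe* and no criterion. No other section mentions death, hospitalisation, prolonged stay, disability or medical importance as a ground for calling an event an SAE.

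**Step 2: the rules that depend on it.** Take an event that leads to admission or lasting disability but does not threaten life.

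| Rule in the safety section | Condition in the text | Triggered by this event as written? | Triggered under an outcome-based definition? |
|---|---|---|---|
| Documentation | any adverse event | yes | yes |
| Notice to chief investigator within 24 hours | SAE | no | yes |
| Report to ethics committee | SAE, judged related | no | yes, if related |
| Report within 15 days | SAE, related and unexpected | no | yes, if related and unexpected |
| Local reporting | SAE, as the local bodies require | no | yes, as those bodies require |

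The clearest loss is the 24-hour notice, which carries no further condition. The ethics-committee report is lost only for related events, and the 15-day report only for events that are also unexpected.

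**Step 3: does the general sentence close the gap?** The instruction that all adverse events be documented and the reporting procedures followed might seem to carry every event into the escalation steps. It does not, because each timed or ethics-committee step is itself limited to SAEs. For any other adverse event, documentation is the only specific duty left.

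**Step 4: fatal events.** Death is not listed. An event that proves fatal would nevertheless ordinarily be read as life-threatening, so most deaths would probably be escalated. The definition should name death, but the gap does not rest on it.

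**Step 5: effect on data.** The adverse-event definition covers any undesirable medical experience, related or not, and all such events are to be documented. An admission or injury below the SAE threshold is therefore still on record. The harms named under Secondary outcomes, bruising and phlebitis at 2 weeks by clinical examination, do not use the SAE label.

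**The case against.** **The article is a condensed text.** The safety section points to a national SAE form, to local ethics-committee, sponsor and research-office requirements, and to the compliance office's monitoring policies. Any of these, or the full protocol, may hold a wider definition that staff actually used. This stands as a limit: the article cannot show that conduct was affected. It does not remove the point, because the article does not leave the definition to another document. It states one. If a wider one exists, the two conflict and must be reconciled.

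**The standard comes from outside the document.** The distinction between *serious* and *severe*, and the list of outcomes, are general trial practice and are not in the article. That is so. The consequence in the table nevertheless follows from the article's own wording.

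**Four stronger readings are tempting, and the document does not support them.**

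- *Deaths go unreported.* An ordinary reading of life-threatening takes in an event that kills.
- *The comparison of safety between arms is lost.* All adverse events are to be documented, so the data for a comparison remain.
- *Unblinded grading biases the SAE count by arm.* Under Blinding, patients and the clinical team know the allocation at the intervention, but the clinicians at follow-up reviews and the duplex scan are blinded. Patient reports and events around the procedure may still be open to influence. Nothing shows, though, that a one-criterion definition would make grading differ by arm.
- *Most serious events would be missed.* The article gives no event or admission rates, so no share can be stated.

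**It has no bearing on the efficacy result.** This is correct, and it limits the weight of the point.

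**Conclusion.** The point holds for events that hospitalise, prolong a stay or lastingly disable without threatening life. As the article is worded, they are documented but trigger neither the 24-hour notice nor, where the further conditions are met, the ethics-committee and 15-day reports. This is a rule that is stated and stated too narrowly, not a detail left to another document.

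The size cannot be quantified. In a trial planned for 160 patients the number of affected events could be small, including none, and the article offers no basis for an estimate. The planned re-intervention comparison, the sample size and the recording of adverse events do not change.

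The conclusion assumes that staff apply the definition as written and that no wider definition in the full protocol or sponsor policy overrides it. It is a correction the sponsor should make for participant protection and for clear safety reporting. It is not a threat to the trial's main result.

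**What to change.** 1. In the safety section and in the abbreviation list, change *severe* to *serious*.
2. Replace the one-criterion sentence with a definition by outcome: an adverse event that results in death, is life-threatening, requires or prolongs hospitalisation, results in persistent or significant disability, or is otherwise medically important.
3. Check that wording against the SAE form and the sponsor policy that the section cites, so that one definition governs all the reporting steps.
4. Leave the conditions on relatedness and expectedness as they are. The problem lies in the definition that feeds them.

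The cost is one rewritten sentence, one word changed wherever the term is spelled out, and slightly more expedited reporting. No redesign, extra patients or change to the analysis is needed.
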